**Planned statistical analyses**

All children in both arms will be included in the analysis (i.e., an intent-to-treat analysis). Preliminary analyses will include descriptive statistics (means and standard deviations for continuous variables; frequencies for categorical variables) for all measurements in each intervention group separately. Gender-disaggregated data will be presented in tables, whenever pertinent.

Multivariate analyses will be used to compare the post-deworming (at 4-months) STH re-infection rates between the two groups. To account for the within-school clustering, hierarchical (random effects) logistic regression models will be used [41]. The model will include important confounding variables such as gender, sex, age, school ecological zone, as well as any baseline characteristics that may not be balanced between the two groups. Subgroup analysis will be performed for boys and girls separately as well as for each of the three helminth species studied (*Ascaris*, *Trichuris*, and hookworm).

All statistical tests will be two-sided and a 0.05 level of significance will be used throughout for determination of statistical significance. Point estimates of the intervention effect with 95% confidence intervals will be presented to demonstrate the precision of the study results.

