**Methods**

**Study design**

A prospective cluster-randomized controlled trial design will be used (Figure 1). Schools will be randomly allocated to one of the two arms using a stratified randomization technique (by school size). Because the total number of students enrolled in Grade 5 varies from 20 to more than 200 per school, the stratified design will ensure a balanced proportion of children in each of the two arms. A simple baseline questionnaire will be administered to all Grade 5 students to collect information on gender-specific risk factors and to evaluate the level of knowledge regarding STH infections. Each child will be weighed and measured (for anthropometric measures), and a stool specimen will be collected and examined for STH eggs (to estimate STH infection rates and intensity). The health hygiene education intervention will begin immediately after the routine deworming program in schools in the intervention arm. Schools in the control arm will follow their standard curriculum. (These schools will be offered the health hygiene education intervention after the 4-month follow-up period.)

Two weeks after the deworming, an efficacy assessment will be undertaken in a sub-sample of 300 previously-infected children (ie. Stool specimens will be collected to estimate cure rates for each STH. This is needed to provide a correction factor in the data analyses.). At the end of the 4-month follow-up study period, the baseline questionnaire will be re-administered to all children in both arms, the children will be weighed and measured, and re-infection rates will be assessed by collecting a stool specimen from each child. Absenteeism rates, based on routine school records, will be assessed from baseline to the end of the follow-up period. An intention-to-treat analysis will be used to compare outcomes in the two arms.

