**Study population**

Multidisciplinary and participatory workshops conducted to ascertain local health priorities in the urban slum of Belén demonstrated that intestinal parasites were among the top-five health priorities and that targeted health hygiene education interventions were required [1]. In fact, in a recent survey we conducted in Belén, we found 86% of Grade 5 school children infected by at least one STH species (*Ascaris*=60.4%, *Trichuris*=77.9%, and hookworm=21.2%) [2].

We have obtained current information on the number of children enrolled in Grade 5 in schools of Belén, Peru. For efficiency purposes, only schools with a minimum enrolment of 10 boys and 10 girls in Grade 5 will be considered eligible. Eighteen schools, totalling more than 1438 students, are therefore considered eligible to participate in this trial.

*Inclusion criteria*

- Girls and boys enrolled in Grade 5 in one of the 18 eligible schools in Belén.
- Informed written consent obtained from the parents or legal guardian of the child.
- Verbal assent from child.

*Exclusion criteria*

- Parents (or guardians) refusing participation of their child.
- Child who refuses to participate.

[figure not shown]

Figure 1: Flowchart of the cluster-randomized controlled trial

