**Measurements**

Weight of the child will be measured using a portable flat scale (seca 869, seca corp., Baltimore, MD) and a mobile stadiometer (seca 217, seca corp., Baltimore, MD) will be used to measure their height. Individual risk factors, potential confounding variables, level of knowledge on STH transmission, and behavioural determinants will be measured using an interviewer-administered questionnaire at baseline. After the 4-month follow-up period, the same questionnaire will be re-administered.

Stool specimens will be obtained in small plastic containers at baseline and at the end of the 4-month follow-up period by trained research personnel. Trained technologists will use the Kato-Katz method to examine the specimens for the presence, species and intensity of STH eggs [37]. This technique is the preferred method for assessment of the prevalence and intensity of intestinal parasitic infections in the field [4, 38]. The technologists will be blinded to the group assignment.

Data collection activities during fieldwork will be regularly supervised. Measurement bias will be kept to a minimum by ensuring calibration of study instruments (balance and scale), quality control assessments, and daily review of completed questionnaires. At each assessment, the coordinator will check all completed forms immediately after data collection at the end of each day. Entries on the questionnaires will be checked and if discrepancies or unclear answers appear, a discussion and explanation of the question and eligible answers will take place to avoid making errors the next day. Corrections will be made, if warranted. These types of errors should be kept to a minimum, as there will be a pre-testing phase with all interviewers to ensure correct data collection procedures and records. The consistency of the microscopic readings will be verified both during the examination and afterward as follows. The consistency of egg counting will be evaluated among the laboratory technologists using standard quality control methods [38]. The laboratory supervisor will read 10% of the slides of each microscopist without prior knowledge of the results. In the case of a discrepancy larger than 10%, the two readers will discuss the slides and further slides will be examined to avoid repeated errors. It should be noted that trained microscopists from our previous study will perform the examinations. They have an excellent performance record.

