**Sample size justification**

Based on our survey of schools in Belén, 18 schools are eligible and have already demonstrated an interest in participating in the study. They have a total of 1438 students enrolled in Grade 5 (Table 2). Power calculations are based on the formula for logistic regression with a single binary covariate (i.e. the education intervention) and the Wald test was used as the basis for computations [39]. Based on our past parasitological Belén school surveys a response rate of 80.6% is expected [2]. A 5% loss to follow-up is also assumed during the 4-month period. Thus, we estimate a sample size of 1101 participating students, distributed in the 18 schools.

In addition, the power calculations must take into account within-school clustering. The intraclass correlation coefficient (ICC) represents the proportion of the total variance that is accounted for by between-cluster rather than within-cluster variation and can be used to calculate the Effective Sample Size (ESS). Because we could not find any reported ICC of within-school clustering of STH re-infection in the literature, we re-analysed the original database of [name] et al. [2], which contained the parasitological results of 1074 Belén students, and calculated the within-school ICC of STH prevalence (as an estimation of ICC of re-infection rates). The ICC was calculated using STH prevalence as the outcome and the school as the grouping factor, while adjusting for age, sex, and the school ecological zone (floodplain or upland). The obtained ICC had a value of 0.028 which resulted in an ESS of 412 and an associated design effect of 2.7. Power was estimated assuming that 50% of children will be exposed to the intervention and that the re-infection rate in the control group will be 49.5%. The latter is based on the reported 3-month re-infection rate of Malaysian school-children treated with albendazole [40]. Thus, the proposed study has good power (80.3%) to detect a moderate effect (i.e., OR=1.75) and has an excellent power (93.4%) to detect a strong effect, corresponding to an OR of 2.00.

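### The re-infection model adds any baseline item that looks unbalanced, with no criterion, while baseline STH status and the school-size stratum have no assured place in it

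*Protocol*

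**What the plan says.** Under Planned statistical analyses, re-infection at 4 months is compared between arms with multivariate models, and to allow for clustering "hierarchical (random effects) logistic regression models will be used". On covariates: "The model will include important confounding variables such as gender, sex, age, school ecological zone", followed by "as well as any baseline characteristics that may not be balanced between the two groups". No threshold, test or candidate list is given, and nothing says whether balance is judged across children or across schools.

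Under Study design, schools are allocated to two arms by randomisation stratified on school size, and each child gives a stool specimen at baseline. Under Measurements, "Trained technologists will use the Kato-Katz method to examine the specimens for the presence, species and intensity of STH eggs". So infection status and egg count by species are known for each child who gives a specimen before deworming. The analysis section names neither of these, nor the school-size stratum, as a covariate.

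**The concern.** The imbalance clause is a selection rule for the main comparison that works only after the arms have been compared at baseline. An observed difference between randomised arms is not evidence that the variable predicts the outcome. A harmless item may enter because of chance, while a prognostic one that happens to be balanced stays out.

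Two things are at stake. First, several adjusted answers become available, and the choice between them rests on how someone reads the baseline table. The model is logistic and odds ratios are non-collapsible: adding a prognostic covariate changes the quantity being estimated even when there is no confounding. The meaning of the reported effect is then not settled in advance. Second, the baseline counterpart of the outcome and the factor used to stratify the randomisation are both available, yet nothing guarantees that the model uses them.

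**Working it through.** **1. The plan's own figures.** Inputs from Sample size justification: 1438 enrolled, 80.6% response, 5% loss, 18 schools, ICC 0.028, control rate 49.5%, half the children exposed.

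- N = 1438 × 0.806 × 0.95 = 1101, as stated.
- Design effect = 1 + (1101/18 − 1) × 0.028 = 2.68 (stated 2.7).
- Effective sample size = 1101/2.68 ≈ 410 (stated 412).
- Wald power = Φ(√N × ln OR / √V − 1.96), with V = 1/(0.5·p1(1−p1)) + 1/(0.5·p0(1−p0)) and N = 412. For OR 1.75, p1 = 0.632 and V ≈ 16.6, so Φ(20.30 × 0.560 / 4.07 − 1.96) ≈ 79.6%. In the protective direction it is 79.4% (stated 80.3%). For OR 2.00 it is 92.6% to 92.8% (stated 93.4%).

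These agree closely and are not in dispute. The intervention is the only covariate in this calculation, so it does not help to choose the others.

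**2. Number of candidates.** The English questionnaire has items 1–22, 26–30 and I–III, that is 22 + 5 + 3 = 30, including weight and height. Sex and age are already in the model; the stool results come on top. About 30 is a fair count.

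**3. Chance imbalance.** For k independent items, each validly tested at 5%, P(at least one flagged) = 1 − 0.95^k.

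- k = 10: 40%
- k = 20: 64%
- k = 30: 79%

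Independence and the 5% test are assumptions; the protocol states no test.

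**4. Illustrative null simulation.** It used the 18 school sizes in Table 2, scaled for response and loss, with size-matched allocation, ICC 0.028 for every item, 20 baseline items and 86% infected at baseline. The imbalance rule was a child-level test at p < 0.05 that ignores clustering. The analysis was a two-stage linear one at cluster level with 16 degrees of freedom, in 1500 trials per setting.

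- At least one of the 20 items was flagged in over 99% of trials.
- Baseline infection was flagged in about 17%.
- Type I error was 3.5% to 5.5% under no, fixed or imbalance-selected adjustment (Monte Carlo standard error √(0.05 × 0.95/1500) ≈ 0.6 percentage points).

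**5. Precision from any-STH status.** SD of the arm difference, unadjusted against prespecified adjustment for binary baseline infection, by assumed log odds ratio:

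- 0.5: 0.0485 to 0.0483, about 0.6% lower
- 1.0: 0.0486 to 0.0478, about 1.8% lower
- 2.0: 0.0457 to 0.0444, about 2.8% lower

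The gain is small partly because any-STH status varies little: "we found 86% of Grade 5 school children infected by at least one STH species". The same survey gives 60.4% for *Ascaris*, 77.9% for *Trichuris* and 21.2% for hookworm, so species status varies more. The protocol gives no strength of association with later infection, so that gain cannot be computed.

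The SD was lower still under imbalance-selected adjustment. That should not be read as a benefit: the first stage fits the covariates without arm, so adjusting for items correlated with arm pulls the arm difference towards zero.

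**The case against.** Much of the case on the other side stands.

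- **Part of the model is already fixed.** Gender, sex, age and ecological zone are named. Only the additions depend on imbalance.
- **The named list is open-ended.** It is introduced by examples, so baseline infection could enter as a further confounder, and an SAP that is not shown may complete the list. A reader might infer that baseline infection enters only if unbalanced. The text does not say that; it only fails to assure it. An incomplete list alone would be no finding. The finding is that the protocol itself states a data-driven rule.
- **Error rate.** A reader might infer that the rule inflates type I error. The simulation shows no inflation. It did not use the planned random-effects logistic model, and it applied the rule mechanically rather than with an analyst choosing, but nothing in the documents shows inflation.
- **How many covariates enter.** A reader might take the design effect of 2.7, find P(|Z| > 1.96/√2.7 = 1.19) ≈ 0.23 per item and conclude that about 30 × 0.23 ≈ 7 would enter. That needs a significance test the protocol does not state, one that ignores clustering, and an ICC derived only for STH prevalence. With valid 5% tests the expected number is 30 × 0.05 = 1.5.
- **Degrees of freedom.** The added items would be mostly child-level and would not each use up a school-level degree of freedom.

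It can also be said that imbalance need not be pure chance, because the Chronogram places parental consent after randomisation, so uptake could differ by arm. That would be a reason to prespecify prognostic covariates. A rule with no criterion is not a dependable remedy for it.

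None of this supplies the missing criterion or secures a place for the baseline stool result and the stratum.

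**Conclusion.** The point holds in a limited form. The protocol commits its re-infection model to an imbalance-triggered rule with no criterion. With 18 randomised schools and about 30 candidate items, the rule would probably be triggered: about 79% for at least one item, assuming independent items and valid 5% tests. Which adjusted, non-collapsible odds ratio is reported then depends on the allocation draw and on judgement. Baseline parasitology and the school-size stratum have no assured place.

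Bias, type I error inflation and material power loss are not shown. It is tempting to call baseline infection the strongest available predictor and expect a sizeable gain in precision. The protocol gives no figure for that, and for any-STH status the simulated reduction in SD is only about 0.6% to 2.8% under assumed log odds ratios of 0.5 to 2.0. The change is worth making because it removes discretion at almost no cost.

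**What to change.** Delete the imbalance clause and state a short primary model in advance: random-effects logistic regression with school as the random effect, and fixed terms for arm, school-size stratum, ecological zone, age, sex and one chosen baseline STH measure. That measure should be either species-specific infection status or log(eggs per gram + 1), chosen before the arms are compared.

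Name a missing-covariate method that keeps children who lack a baseline specimen in the analysis, in line with the intention-to-treat statement. Move any adjustment for observed imbalances to a sensitivity analysis labelled as such.

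The cost is a few sentences in the analysis section; all the variables are already collected or known. The downsides are slight extra work for missing baseline values and one more school-level term, the size stratum, in a model with 18 schools.

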**Secondary**

The following secondary research objectives will also be addressed: i) to determine intervention effects on absenteeism rates; ii) to assess gender-specific determinants of STH infection, re-infection and absenteeism rates; iii) to measure STH species-specific cure rates and egg reduction rates; and iv) to examine behavioural and social determinants of STH infection, re-infection and absenteeism rates.

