**Health hygiene education intervention**

Lack of knowledge on the transmission and prevention methods of STH infections is common factor in affected population groups of Latin America [27]. Therefore, the specific objectives of the health hygiene education intervention are:

i) To implement a gender-specific health hygiene education strategy which will result in a sustainable intervention that encourages the pro-active role of both teachers and students.

ii) To encourage changes in attitudes and practices with the aim of keeping the level of parasite infection low, through increased knowledge.

iii) To identify modifiable gender-specific behavioural and social determinants which favour the acquisition and transmission of STH infections to inform prevention activities.

Workshops will be organized for and by Grade 5 teachers to train them on the health hygiene education strategy. The education material will be provided by the Pan American Health Organization (in Spanish) and will be adapted to the local culture. The health hygiene education intervention will take into account the gender-specific perceptions, values, social constructs, and beliefs of students and teachers relevant to STH infections in order to maximize behavioural changes. After the workshop, Grade 5 teachers will be able to implement the health hygiene education intervention in their classroom and engage their students. Bi-monthly visits with the teacher by our research team and once monthly with the class will be performed to monitor the application of the education program during the 4-month follow-up period. Specifically, the intention of the health hygiene education program is to modify key gender-specific modifiable behavioural determinants that have been shown to be associated with STH infections from our review of the literature:

i) Not using soap for hand washing [28-30]

ii) Not hand washing (no reference to the use of soap) [31-33]

iii) Eating unpeeled or unwashed fruits [31, 34]

iv) Walking barefoot [30, 33]

v) Open air defecation [33-35]

vi) General unhygienic behaviours [36]

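### The only sex analysis of the intervention effect that the protocol specifies is separate boys-only and girls-only analyses at 0.05, with no arm-by-sex interaction named; these cannot show whether the effect differs by sex.

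*Protocol*

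**What the plan says.** The Protocol's section Planned statistical analyses compares 4-month re-infection between arms with a hierarchical (random effects) logistic model. Sex appears in that model as an adjustment variable: "The model will include important confounding variables such as gender, sex, age, school ecological zone". For the effect by sex, the section says: "Subgroup analysis will be performed for boys and girls separately as well as for each of the three helminth species studied". On testing it says: "All statistical tests will be two-sided and a 0.05 level of significance will be used throughout for determination of statistical significance". It then adds: "Point estimates of the intervention effect with 95% confidence intervals will be presented to demonstrate the precision of the study results".

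No arm-by-sex term is named anywhere in the protocol, and no rule is given for concluding that the effect differs between boys and girls.

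Two other places bear on sex. The first aim of the education programme begins: "To implement a gender-specific health hygiene education strategy". The second of the secondary objectives is "to assess gender-specific determinants of STH infection, re-infection and absenteeism rates", which concerns determinants and does not ask whether sex modifies the intervention effect.

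**The concern.** Because the programme is designed to be gender-specific, readers will set the boys' result beside the girls' result and ask whether they differ. The specified analysis cannot answer that. A p-value below 0.05 in one sex and above it in the other is not evidence of a difference. Each half-sample has clearly less power than the whole trial, so such a split will be fairly common even when the effect is the same in both sexes.

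The Executive summary says the results will inform school deworming programmes in Peru and elsewhere. A mistaken message that hygiene education works only for girls, or only for boys, could therefore affect how programmes are designed.

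**Working it through.** **Inputs** (Protocol, Sample size justification and Table 2): 1438 children enrolled in 18 schools, 80.6% response, 5% loss to follow-up, intraclass correlation (ICC) 0.028, effective sample size (ESS) 412, design effect 2.7, half the children exposed, control re-infection 49.5%, power 80.3% at OR 1.75 and 93.4% at OR 2.00.

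**Assumptions not in the documents:** a 50:50 sex split, the same control rate in both sexes, and the extent to which boys and girls in one school share the school effect. The last is shown as a range from none to complete. The ORs are taken in the protective direction (1/1.75 and 1/2.00).

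**Step 1. Reproduce the protocol's figures.**
- N = 1438 × 0.806 × 0.95 = 1101.
- Mean school size = 1101/18 = 61.2. Design effect = 1 + (61.2 − 1) × 0.028 = 2.68. ESS = 1101/2.68 = 410 (stated 412).
- SE of ln OR = √[1/(206 × 0.495 × 0.505) + 1/(206 × p₁ × (1 − p₁))], with 206 = 412/2 per arm.
- For OR 1/1.75, p₁ = 0.359 and SE = 0.201. Power = Φ(0.560/0.201 − 1.96) = 79.4%. For OR 1/2.00, power = 92.6%. A two-proportion formula gives 79.9% and 93.1%. These agree closely with 80.3% and 93.4%.

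**Step 2. Effective sample size per sex.** Simply halving 412 would be too harsh, because clusters of half the size have a smaller design effect. Two versions are used.
- Equal schools: 1101/2 = 550.5 children per sex, 30.6 per school. Design effect = 1 + (30.6 − 1) × 0.028 = 1.83. ESS = 550.5/1.83 = 301.
- Actual school sizes: each 2008 enrolment in Table 2 × 1101/1438 ÷ 2 gives mᵢ. ESS = Σ mᵢ/(1 + (mᵢ − 1) × 0.028) = 267. (The same formula on the whole trial gives 365, against the protocol's 412.)

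**Step 3. Probability that exactly one sex reaches p<0.05 when the true effect is identical.** If the two tests are independent, this is 2 × power × (1 − power). If the school effect is fully shared, the two estimates are correlated. For equal schools the correlation is (0.028/18)/(1.83/550.5) = 0.47, and for the actual sizes it is 0.48. The probability then comes from the bivariate normal distribution.

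| True OR | School sizes | Power per sex | Split, independent | Split, fully shared |
|---|---|---|---|---|
| 1.75 | equal (ESS 301) | 66% | 45% | 31% |
| 1.75 | actual (ESS 267) | 61% | 48% | 33% |
| 2.00 | equal (ESS 301) | 83% | 28% | 21% |
| 2.00 | actual (ESS 267) | 78% | 34% | 24% |
| no effect | either | 5% | 9.5% | about 8% |

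For example, at ESS 267 and OR 1.75: 2 × 0.61 × 0.39 = 0.476.

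**Step 4. An interaction test in the same settings.** With no true sex difference it rejects in 5% of trials by construction (simulated 4.97 to 4.99%).

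Its power is limited. Take OR 1.75 in one sex and no effect in the other, at ESS 267. The per-sex SEs are 0.250 and 0.245.
- Independent estimates: the SE of the difference is √(0.250² + 0.245²) = 0.350, and power is Φ(0.560/0.350 − 1.96) = 36%.
- Fully shared school effects (correlation 0.48): the SE falls to 0.252 and power is about 60%.
- At ESS 301 the corresponding figures are about 40% and 64%.

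**The case against.** A reader might infer that the trial will declare a sex difference by comparing the two subgroup p-values. The protocol does not say so. It states no such rule, no objective asks for a between-sex contrast of the intervention effect, and it commits to point estimates with 95% confidence intervals. Sex-specific estimates are legitimate reporting and do not exclude an interaction test. A statistical analysis plan that is not at hand may contain one, so its absence from the protocol does not prove that none is intended. All of this stands, and it limits the point to what the protocol specifies. It does not remove the point. The protocol chose a method, splitting the sample by sex, and two separate intervals still do not give an interval for the difference.

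A reader might also take the 48% as the expected rate. It is the top of the range: OR 1.75, unequal schools and independent tests. Boys and girls attend the same randomised schools, so full independence is implausible and the lower figures deserve equal weight. With no effect the rate is only about 8 to 9.5%. Nor is the split rate the error rate of a planned test; it measures how often the results would invite a misreading, so setting it beside 5% is an illustration and not a like-for-like comparison.

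The same sentence of the protocol also calls the three helminth species subgroups. They are separate outcomes in the same children. That is loose wording, and whether they should share the 0.05 level is a matter of preference on multiplicity. Neither is part of this point.

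**Conclusion.** The point holds in limited form. The one analysis of the intervention effect by sex that the protocol specifies cannot show whether the effect differs by sex. If the intervention works equally in both sexes at the planned effect sizes, exactly one sex would be significant in about 21 to 48% of trials, depending on the OR and on how far school effects are shared. This rests on the assumptions listed in the working and on normal approximations. It does not establish that a false sex difference will be claimed. The matter is minor: the primary comparison is unaffected, and the remedy is a better method at almost no cost.

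**What to change.** Replace the separate boys-only and girls-only analyses with one hierarchical logistic model on all children, adding an arm-by-sex term to the model already planned. Report the interaction OR with its 95% CI and p-value, and give the sex-specific intervention ORs with CIs from that same model. State that any conclusion about a sex difference will rest only on the interaction estimate.

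The cost is a change of wording and one model term, with no extra children, visits or data. The drawback is the limited power shown in the working: a non-significant interaction would not show that the effect is the same in boys and girls, and its interval should be read accordingly.
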